#### 2.3.2. Cord Blood

Within 30 min of birth, 5 mL of arterial whole blood will be collected from the umbilical cord by puncturing the artery with a needle. From this, 500 µL will be transferred into BD Vacutainer^®^ plastic whole blood tubes with spray-coated K2 potassium salt of ethylene diamine tetra acetic acid (EDTA) (BD, Franklin Lakes, NJ, USA), and one drop will be used to collect a 10 µL sample with the volumetric absorptive microsampling (VAMS) kit. The VAMS devices will be obtained from Neoteryx (Torrance, CA, USA).

The remaining blood will be transferred into a 4 mL EDTA tube and then further transferred to two 2 mL sterile cryotubes (Biosigma, Cona, VE, Italy) after gently mixing by tilting it ten times. The 500 µL microtainer EDTA tube, 10 µL VAMS, and the two 2 mL cryotubes will be stored at −80 °C until transfer to the designated laboratories for analysis.

The 500 µL samples will be centrifuged using a microcentrifuge (VWR International, Leuven, Belgium) to obtain plasma samples, which will be used for cytokines and chemokines, immunophenotyping, and proteomics analysis. The two 2 mL samples will be used for black carbon, mitochondrial DNA content, and telomere length analyses using a previously validated method [32]. The 10 µL VAMS will be used for untargeted metabolomics analysis.

#### 2.3.3. Capillary Blood

Capillary blood samples will be collected from mothers on the day of delivery and from infants at Dol 1, 3, 4, 7, 30, and 60. The collection zones for mothers are fingers, and for infants are heels. A total of 500 µL of blood will be collected from the incision site onto an EDTA microtainer tube. After this, 40 µL and 20 µL of blood samples will be collected using the VAMS kit. The 500 µL microtainer EDTA tube and VAMS samples will be stored at −80 °C before they are transferred to laboratories.

The 500 µL samples will be centrifugated to obtain plasma samples for cytokines and chemokines, immunophenotyping, and proteomics analysis. The 20 µL VAMS will be used for mycotoxins analysis, and the 10 µL VAMS will be used for untargeted metabolomics analysis.

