#### 2.4.2. Immunophenotyping

Immunophenotyping from blood samples will be conducted using flow cytometry, analyzing T cells, B cells, Monocytes, NK cells, DCs, and granulocytes. This will include the following analysis:Analysis of B cell subsets (transitional, naive, memory, plasma blasts);Analysis of T cell subsets (naive, memory, effector);Analysis of T cell activation state (activated, exhausted);Analysis of T helper cell differentiation (Tregs, Th1 and Th17);Analysis of monocyte subsets (classical, inflammatory, and patrolling);Analysis of DC subsets (plasmacytoid DCs, cDC2, and cDC3);Analysis of granulocytes (neutrophils, basophils, eosinophils);Analysis of granulocyte maturation;Analysis of activation markers (CD64, HLA-DR, CD25, CD38); and,Analysis of NK cell subsets (CD56 and CD16 populations).

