**Blood**																
Plasma (cytokines and chemokines)				D ^1^	B		B		B		B			B	B	
Plasma (immunophenotyping)				D ^1^	B		B		B		B			B	B	
Plasma (proteomics)				D ^1^	B		B		B		B			B	B	
Whole blood (black carbon exposure)				B ^1^												
Whole blood (mitochondrial DNA, telomere length)				B ^1^												
Whole blood on VAMS (mycotoxins)				M							B		B			
Whole blood on VAMS (untargeted metabolomics)				D ^1^	B		B		B		B					

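### Immunophenotyping is assigned to plasma, but it is defined as flow cytometry of leukocytes, so no described blood aliquot can serve it as written

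*Protocol article*

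**What the plan says.** Three places in the protocol article name plasma as the immunophenotyping material.

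- Section 2.3.3 (capillary blood): the 500 µL "samples will be centrifugated to obtain plasma samples for cytokines and chemokines, immunophenotyping, and proteomics analysis".
- Section 2.3.2 (cord blood): the 500 µL EDTA sample is centrifuged to plasma, "which will be used for cytokines and chemokines, immunophenotyping, and proteomics analysis".
- Table 3, Blood block: a row whose label begins "Plasma (immunophenotyping".

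Section 2.4.2 defines the assay: "Immunophenotyping from blood samples will be conducted using flow cytometry, analyzing T cells, B cells, Monocytes, NK cells, DCs, and granulocytes". It goes on to list subsets, activation states and granulocyte maturation.

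On storage, section 2.3.3 says the "microtainer EDTA tube and VAMS samples will be stored at −80 °C before they are transferred to laboratories". Section 2.3.2 says the EDTA tube, the VAMS sample "and the two 2 mL cryotubes will be stored at −80 °C until transfer to the designated laboratories for analysis". In both sections centrifugation first appears in the paragraph after the one on storage.

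**The concern.** Plasma is what remains once the blood cells have been removed. Flow cytometry of T cells, B cells, monocytes, NK cells, dendritic cells and granulocytes measures only cells. The material named three times therefore cannot support the assay defined in section 2.4.2.

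The immune system is one of the three bio-networks in the study's first objective, and section 3 lists immunophenotyping among the domains that set the study apart. A site that followed the article literally would hold no analysable cell specimen. Blood from birth and the first week cannot be drawn again later.

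The order of storage and spinning raises a separate question. The same EDTA tube supplies the cytokine and chemokine assays and the proteomics, so its handling before freezing matters for those results too.

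**Working it through.** The plan gives no figure to reproduce here. The check follows each blood aliquot from collection to assay.

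**Aliquots and stated uses (sections 2.3.2 and 2.3.3)**

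1. 500 µL EDTA tube, cord and capillary: stored at −80 °C; centrifuged to plasma; used for cytokines and chemokines, immunophenotyping and proteomics.
2. Two 2 mL cord cryotubes: stored at −80 °C; used for black carbon, mitochondrial DNA and telomere length.
3. VAMS samples: stored at −80 °C; used for untargeted metabolomics and, for capillary blood, mycotoxins.

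Aliquots allotted to fresh, fixed or cryopreserved cells: 0. Places that name plasma for immunophenotyping: 3 (sections 2.3.2 and 2.3.3, and Table 3). Section 2.4.2 speaks only of blood samples and identifies no further aliquot.

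**Number of samples affected**

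- Infant time points in the Table 3 row: birth (cord), Dol 1, 3, 5, 7, 30 and 60, so 1 + 6 = 7.
- Section 2.3.3 lists Dol 4 where Table 3 has Dol 5. The count is 7 on either list.
- Target in section 2.1: 140 dyads. Planned maximum: 7 × 140 = 980 infant samples. With the 141 pairs given in the Abstract it would be 7 × 141 = 987.
- Mothers: one capillary sample on the day of delivery, so up to 140 more.

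These are ceilings. They assume that every infant is sampled at every visit, with no loss to follow-up, death or failed draw.

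**Order of centrifugation and freezing**

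The article does not say whether tubes are spun before freezing or after thawing. There are two cases:

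- *Frozen unseparated, spun after thawing.* Whole blood frozen without a cryoprotectant lyses. The supernatant would carry cell contents into the cytokine, chemokine and proteomic readouts, and no intact cells would remain.
- *Spun first, plasma frozen.* The plasma readouts are not affected in this way. The conflict over immunophenotyping remains, because plasma still holds no cells.

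**The case against.** The strongest reply is that this is loose labelling in a condensed article. Section 2.4.2 refers to blood samples, not plasma. One EDTA tube feeds all three assays, so plasma may simply be shorthand for that tube. Section 2.3.8 places detailed instructions and standard operating procedures in the Supplementary Materials, which are not at hand. Section 2.3 also leaves out pre-freezing steps given elsewhere: sections 2.4.10 and 2.4.12 mention snap-freezing of cord blood and placenta, while 2.3.2 and 2.3.4 do not. Silence about an early spin or a cell aliquot is therefore weak evidence that neither exists.

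Much of this stands. The absence of a fixation or stabilisation step is not in itself a finding, and the contamination question can only be put conditionally. The reply does not remove the contradiction, because plasma is what the article states, in three places. If the supplementary procedures describe a proper cell aliquot, the article contradicts them and still needs correcting.

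A reader might go further and infer that the plasma assays are certainly contaminated, or that artefactual differences between SVNs and controls would follow. The documents support neither. They do not say that spinning follows thawing, and they give nothing on how released cell content would vary with gestational age or day of life.

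**Conclusion.** The contradiction over the immunophenotyping material holds and has to be resolved. As written, an entire class of stated immune measurements, up to 980 planned infant samples plus the maternal delivery sample, has no cellular specimen. This rests only on the article's own text and on the meaning of plasma.

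It does not show that flow cytometry will fail in practice. The article cannot distinguish a wrong label from an unworkable workflow, and the unseen procedures may already provide for cells.

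The risk to the cytokine and proteomic readouts is a second, conditional point. It applies only if EDTA tubes are frozen unseparated and spun after thawing.

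**What to change.** - In sections 2.3.2 and 2.3.3, state that a cell-containing portion of the existing draw is set aside and preserved for flow cytometry before freezing. Leave the choice of preservative and the aliquot volumes to the laboratory.
- In the same sections, state that the remainder is centrifuged to plasma before storage at −80 °C.
- In Table 3, rename the immunophenotyping row after the cell-containing specimen.
- Reconcile these passages with section 2.4.2 and the supplementary procedures, and settle whether the early sample falls on Dol 4 or Dol 5.
- Flag any tube already frozen unseparated, exclude it from cell phenotyping, and check in a sensitivity analysis whether its plasma readouts differ from those of tubes spun first.

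If the supplementary procedures already work this way, only the wording changes. Otherwise the cost is same-day processing and less plasma from each 500 µL sample, with no increase in the volume drawn. The article gives no minimum volumes for the plasma assays, so the laboratories must confirm that the remaining plasma is enough.

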#### 2.3.4. Placental Biopsy

The placenta will be placed on a tray with the fetal side facing up, and then any excess blood will be cleaned off using phosphate-buffered saline-soaked sterile gauze. An area approximately 2 cm from the umbilical cord, between the large veins, will be identified for sampling. A 1.5 cm deep strip of placental tissue will be cut using the scalpel sleeve. Two tissue samples will be collected, with each sample dipped into a phosphate-buffered saline-filled falcon tube and shaken gently to remove maternal blood. This process will be repeated three times, and the cleaned samples will then be placed into two 2 mL cryotubes. Samples will be stored in a −80 °C freezer before they are transferred to the laboratory. The placental samples will be used for DNA adductomics analysis.

#### 2.3.5. Vaginal Samples

Vaginal samples will be collected at 29–30 weeks and 33–34 weeks of gestation and on the day of delivery using sterile swabs. The sampling is performed by gently scraping both vaginal walls in circular motions for at least 20 s. The swab will be inserted into a 2 mL cryotube, cut to fit, and the tube will be tightly sealed. On the day of delivery, before membrane rupture, an OMR-130 kit (DNA Genotek^®^ Ottawa, ON, Canada) will also be used to collect vaginal samples following the same swabbing process. The samples will then be inserted into the stabilizing liquid tube and sealed. The samples will be stored in the −80 °C freezer before they are transferred to the laboratory. These swab samples will be used for cytokines and chemokines analyses, and the OMR-130 kit samples will be used for vaginal metagenomic analysis.

#### 2.3.6. Breastmilk Samples

Colostrum samples will be collected by manual expression at Dol0 or Dol1 at four intervals within the first 24 h postpartum, and transitional milk will be collected by manual expression at Dol 3 and 5 at one-time point. The healthcare worker will ask the participant which breast was last used for breastfeeding and prepare the opposite breast for collection. For colostrum, a total of 10 mL samples will be collected by manual expression, and then the samples will be transferred into four 2 mL cryotubes. For transitional and mature milk, samples will be collected at Dol7, 14, 30, and 60 using an electric breast pump (Medela, Baar, Switzerland). Samples from the opposite breast last used for feeding will be fully expressed into a 150 mL container, then transferred into four 2 mL cryotubes. If less than 25 mL is collected, the second breast will be expressed. All milk samples will be snap-frozen within 4 h in liquid nitrogen for transfer to the local storage facility, where they will be kept at −80 °C until they are transferred to partner laboratories for analysis.

#### 2.3.7. Saliva Samples

Saliva samples will be collected from mothers and infants at Dol1, 2, 3, 4, 5, 14, and 15. The deuterium oxide (D_2_O) method is used to assess breastmilk intake in infants and to assess body composition in mothers. An oral administration of a small dose of deuterium oxide will be given to the mothers after collecting pre-dose saliva samples at Dol1, and post-dose samples will be collected on Dol2, 3, 4, 5, 14, and 15. To collect saliva samples, mothers will be asked to chew a cotton ball for 2 min, and for infants, trained study staff will use a cotton ball around a straw to collect saliva from inside of their cheeks. After that, saliva will be extracted from cryotubes (20 mL for mothers and 10 mL for infants) using syringes. Samples will be stored in the −80 °C freezer before they are transferred to the laboratory.

#### 2.3.8. Stool Samples

Maternal stool samples will be collected at 24–30 weeks, 33–34 weeks of gestation, on Dol7, 30, 60, and 180 using a stool collection container, and infant stool samples will be collected daily after birth until Dol7, and on Dol 15, 30, 60 and 180 using a sterile protection sheet, wrapped around the infant, functioning like a diaper. After collection, samples will be aliquoted into four 2 mL sterile cryotubes and stored in the −80 °C freezer before they are transferred to the laboratory. Stool samples will be used for shotgun metagenomics, untargeted proteomics and metabolomics analyses, and enteropathogen analysis.

For all detailed instructions and standard operating procedures related to sample collection, refer to the Supplementary Materials.

### 2.4. Laboratory Analysis

#### 2.4.1. Cytokine and Chemokine Analyses

Cytokine and chemokine analyses will be performed on plasma and vaginal samples. Cytokine, chemokine, and immunological biomarkers from plasma samples will be characterized using electrochemiluminescence and the NULISAseq 250-plex inflammation panel [33], including key analytes critical to the inflammation response, immune system regulation, and various related biological processes. 

Cytokines in vaginal or cervicovaginal secretions previously associated with preterm birth will be assessed, including IL-1β, IL-6, IL-17A, and IL-8 [34,35,36,37,38]. In addition, IP-10, a chemokine actively downregulated by dysbiotic microbiota associated with bacterial vaginosis (BV), will be assayed. Concentrations will be measured from lateral vaginal wall swabs using a customized R&D system 6-plex assay, which includes inflammatory (IL-1α, IL-1β, IL-6), adaptive (IL-17A) cytokines, and chemokines (IL-8, IP-10).

#### 2.4.2. Immunophenotyping

Immunophenotyping from blood samples will be conducted using flow cytometry, analyzing T cells, B cells, Monocytes, NK cells, DCs, and granulocytes. This will include the following analysis:Analysis of B cell subsets (transitional, naive, memory, plasma blasts);Analysis of T cell subsets (naive, memory, effector);Analysis of T cell activation state (activated, exhausted);Analysis of T helper cell differentiation (Tregs, Th1 and Th17);Analysis of monocyte subsets (classical, inflammatory, and patrolling);Analysis of DC subsets (plasmacytoid DCs, cDC2, and cDC3);Analysis of granulocytes (neutrophils, basophils, eosinophils);Analysis of granulocyte maturation;Analysis of activation markers (CD64, HLA-DR, CD25, CD38); and,Analysis of NK cell subsets (CD56 and CD16 populations).

#### 2.4.3. Microbiome Composition and Functionality Analyses

Microbiome composition and functionality will be characterized in vaginal, breastmilk, and stool samples.

Microbial communities from these body sites will be characterized using shotgun metagenomic sequencing [39], a high-throughput sequencing approach that enables comprehensive profiling by sequencing all DNA present in a sample. This method allows for the identification of microbial species and strains, as well as functional profiling through the detection of genes associated with specific pathways. DNA extraction will be carried out following standardized protocols to ensure high-quality input for library preparation. Sequencing will be performed using the Illumina platform, which generates paired-end reads with high accuracy and depth. Bioinformatic analysis will include quality control, assembly, taxonomic classification, and functional annotation.

#### 2.4.4. TaqMan Array Card for Enteropathogen Detection

Enteropathogen detection will be conducted using the TaqMan Array Card (TAC) system in a 384-well real-time PCR format to detect 62 infection targets, including viruses, bacteria, protozoa, and helminths, specifically: *A. duodenale* and *lumbricoides*; *B. fragilis* and *hominis*; *C. belli*, *cayetanensis*, *coli*, *concisus*, *difficile*, *hominis*, *jejuni*, *parvum*, *troglodytis*, and *upsaliensis*; *E. bieneusi* and *histolytica*; *G. lamblia*; *H. pylori*; *M. tuberculosis*; *N. americanus*; *P. shigelloides*; *S. enterica*, *flexneri*, *mansoni*, *sonnei*, and *stercoralis*; *T. solium* and *trichiura*; *V. cholerae*; *enteroaggregative E. coli* [*EAEC* (*aaiC*, *aatA*, and *aagR*)], *enteroinvasive E. coli* [EIEC (*Shingella* spp.)], *enteropathogenic E. coli* [EPEC (bfp1 and eae)], *enterotoxigenic E. coli* [ETEC (LT, STh, and STp)], and *Shiga toxin* (stx1 and stx2) producing *E. coli*; *Campylobacter* pan. and *Entamoeba* pan.; *Aeromonas* spp., *Cryptosporidium* spp., *Encephalitozoon* spp., and *Schistosoma* spp.; *adenovirus* (serotypes 40 and 41), *astrovirus*, *Epstein-Barr virus* (EBV), *norovirus* (GI/GII and GI.1/GII.4), *rotavirus*, and *sapovirus*; antibiotic resistance genes, including: β-lactam (CTX-M, TEM, SHV), carbapenemases/carbapenems (KPC, NDM, MCR-1, OXA), macrolide (ermB, mphA), and quinolone (QnrA, QnrB1, QnrB4, QnrS).

#### 2.4.5. Proteomic Analyses

Proteomic analyses will be conducted on blood, breastmilk, and stool samples to comprehensively characterize protein profiles.

Untargeted proteomics analyses for blood and milk samples will be conducted using liquid chromatography-mass spectrometry (LC-MS) on a harmonized Orbitrap ExplorisTM instrument. This system features an EasySpray ion source and is integrated with either an UltiMateTM 3000 Nano LC (Thermo Fisher Scientific, Waltham, MA, USA) or an Evosep system, ensuring high-resolution and reproducible protein identification and quantification. This approach allows for the in-depth exploration of proteomic landscapes in blood and milk samples.

For a subset of stool samples, proteomic analysis will be conducted using mass spectrometry-based methods to identify and quantify proteins in the stool samples, providing insights into microbial and host protein expression [40,41].

#### 2.4.6. Metabolomic Analyses

Metabolomic analyses will be performed on blood, breastmilk, and stool samples to comprehensively assess metabolic profiles.

For blood and breastmilk samples, untargeted metabolomic analyses will be conducted by next-generation rapid liquid chromatography-mass spectrometry (rLC-MS) with a modified Agilent RapidFire 360 sample injector coupled to a high-resolution Agilent 6545B QToF mass spectrometer (Agilent Technologies, Santa Clara, CA, USA). This advanced system integrates the high-throughput separation capabilities of rapid liquid chromatography with the precision and sensitivity of mass spectrometry, enabling the unbiased identification and quantification of a wide array of metabolites.

Metabolomic profiling of a subset of stool samples will also be conducted using LC-MS. This method enables the detection and quantification of metabolites that play critical roles in microbial and host metabolic pathways [40,41].

#### 2.4.7. Breastmilk Analyses

Except for the microbiome, proteomic, and metabolomic analyses described earlier, breastmilk samples will be analyzed for their comprehensive composition using the established International Milk Composition (IMiC) Consortium pipeline. Key components of breastmilk will be quantified as follows:

Macronutrients (lipids, proteins, and carbohydrates) will be measured using near-infrared (NIR) spectroscopy [42], enabling precise quantification of energy-providing nutrients.

Vitamins and minerals will be analyzed using LC-MS and inductively coupled plasma mass spectrometry (ICP-MS), respectively [43].

HMOs and bioactive proteins will be analyzed using LC-MS [43] and electrochemiluminescence (ECL) [44], respectively.

#### 2.4.8. Saliva Analyses

Deuterium oxide concentrations in saliva samples will be measured to assess water turnover and hydration status. This analysis will be conducted by Fourier-transformed infrared (FTIR) spectrophotometry using an Agilent 4500 Series device (Agilent Technologies, Santa Clara, CA, USA). The FTIR spectrophotometer will measure the absorbance of infrared light by deuterium oxide at specific wavelengths. Calibration curves will be constructed using deuterium standards to convert absorbance values into precise concentrations.

#### 2.4.9. Multiple Mycotoxin Profiling

VAMS samples will be used for multiple mycotoxin profiling. Analysis was conducted using a Waters UPLC^®^ system coupled to a Quattro XEVO TQ-XS mass spectrometer (Waters, Manchester, UK). The samples will be detected by UHPLC-MS/MS, which is able to provide the necessary sensitivity at ppb-level [45]. This combination of Ultra-High-Performance Liquid Chromatography (UHPLC) and mass spectrometry ensures robust separation and precise quantification of mycotoxins in blood samples, providing highly accurate and reliable results.

#### 2.4.10. Black Carbon Exposure

Analysis of black carbon will be conducted on umbilical cord blood samples. Two samples of 2 mL arterial umbilical cord blood will be aliquoted, snap-frozen, and stored at −80 °C, then transferred to the University of Hasselt. The samples will be prepared using particle-free instruments and sample holders in a clean room with filtered air to avoid particulate contamination. Black carbon will be detected through non-incandescence-related white-light generation under femtosecond pulsed illumination, as described in previous literature [46].

#### 2.4.11. Telomere Length and Mitochondrial DNA

Telomere length and mitochondrial DNA will be measured via a real-time PCR method using umbilical cord blood [32,47].

Placental and cord blood leukocyte DNA will be extracted using the QIAamp DNA Mini Kit (Qiagen, Inc., Venlo, The Netherlands). DNA quantity and purity will be assessed by a Nanodrop 1000 spectrophotometer (Isogen, Life Science, Belgium). To ensure a uniform DNA input of 5 ng for each qPCR reaction, samples will be diluted and checked using the Quant-iT™ PicoGreen^®^ dsDNA Assay Kit (Invitrogen, Thermo Fisher Scientific, Waltham, MA, USA). Measurements will be performed in triplicate on a 7900HT Fast Real-Time PCR System (Applied Biosystems, Thermo Fisher Scientific, Waltham, MA, USA) in a 384-well format.

